## 9.5 Subgroup analyses

Subgroup comparisons of efficacy, and safety will be conducted by incorporating vaccine-group by subgroup interaction terms into appropriate regression models. Subgroup comparisons will only be conducted if there are at least 5 cases in all subgroups.

Comparisons will include:

1. Males vs females
2. Age (18 to 55 years vs 56-<70 years vs 70+ years)
3. Seropositive to S-spike or non-spike proteins at baseline vs not seropositive
4. Health care workers and highly-exposed participants versus others
5. Standard dose versus low dose

## **9.6 Interim and primary analyses of the primary outcome**

It is planned that the primary evidence of efficacy and safety for the ChAdOx1 nCoV-19 vaccine will be based on global analyses utilizing studies COV001 (the UK P1/2 study), COV002 (the UK P2/3 study), COV003 (the Brazil P3 study) and COV005 (the South Africa P1/2 study) including a pooled analysis across the studies. As such the interim and primary analyses for the primary outcome will be based on cases accumulated across multiple studies, details of which will be specified within the MAA SAP rather than for each individual study. Interim and primary data cuts from this study will therefore be carried out to support the pooled analysis.

The global MAA SAP allows for interim and primary analyses to be conducted once sufficient eligible cases have accumulated, where the overall type 1 error is controlled at the 5% level using a flexible alpha-spending approach that accounts for the incorporation of data from this study into pooled interim analyses under the global MAA SAP.

Evidence of efficacy will be determined if the lower bound of the multiplicity adjusted confidence interval is greater than a 20% threshold. The primary analysis will have approximately 90% power assuming a vaccine efficacy of 60%. A flexible alpha spending approach will be implemented to allow an earlier primary analysis in the situation where accumulation of eligible cases were lower than expected.

Evidence of efficacy at an interim or primary analysis of pooled data will not be considered a reason to stop the trial, but instead will be interpreted as early evidence of efficacy. However if an interim analysis

demonstrates evidence of efficacy then a study level analysis according to the study SAP may be used to support study level evidence of efficacy.

Participants who received other vaccines during the trial will have their vaccination data recorded. If a participant receives an approved or licensed COVID-19 vaccine outside of the trial procedures (such as through their workplace) this information will be recorded. Participants will be censored in the analysis at the time of their vaccination with the alternative COVID-19 vaccine.

If a large proportion of trial volunteers are vaccinated in this way then an exploratory, non-randomised analysis of efficacy according to vaccine(s) received will be undertaken if data are sufficient.

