Those who are eligible (as per government prioritisation strategy) and have been invited to receive an approved or licensed SARS-CoV-2 vaccine can request to be unblinded, all participants will be kept in the study regardless of the combination of COVID-19 vaccines received.

Participants will be asked about the vaccine they received and date of administration which will be recorded along with other vaccines received in a specific externally administered vaccination case report form. Follow up visits will continue as per the participants previous schedule and their data will contribute to ongoing safety monitoring according to the vaccine combinations they have received. Participants will be censored in the analysis of efficacy endpoints at the time of their unblinding and vaccination, but will contribute to exploratory immunological analyses which are descriptive or observational according to the vaccines they have received. When participants have been unblinded they and the GP will receive a letter detailing the vaccines received in the study.

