#### **7.6.1 Unblinding of all trial participants (protocol V19.0)**

All trial participants will be unblinded following the approval of protocol V19.0. This follows the earlier completion of the primary efficacy analysis, the significant level of unblinding that has occurred due to the national vaccine rollout already within the trial and the fall in transmission of SARS-CoV-2 within the UK. Following unblinding and provision of COVID-19 vaccination (in or outside the study), participants will continue to follow all other study procedures and should continue to complete the visit schedule for their group. This will enable further analysis of immunogenicity, safety and immunological correlate of protection analysis.

Provision of treatment for controls is described in section 8.11

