### **8.11 Provision of Treatment for Controls**

If this vaccine is proven to be efficacious following analysis of the primary endpoint and if the DSMB agrees, participants allocated to MenACWY group may be offered the IMP, should extra doses become available.

(Protocol V19.0) Following unblinding, control participants aged 30 and above will be offered ChAdOx1 nCoV-19 in the approved MHRA 4-to-12 week, 2-dose schedule (table 14). Participants will remain enrolled in the study and continue the follow up visit schedule listed for their sub-group *concurrently* with the provision of treatment prime and boost visits.

Due to the updated guidance relating to the emerging association of thrombosis with thrombocytopenia and ChAdOx1 nCoV-19, trial participants aged 29 and under will not be offered (prime) vaccinations with ChAdOx1 nCoV-19. These individuals will instead be advised to await vaccination under the national rollout program.

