## **9.7 Final Analysis**

A final analysis will be conducted at the end of the study. The final study-specific analysis will incorporate all data from the study, including data that has previously contributed to global efficacy estimates under the pooled analysis strategy. The final analysis will be considered a supportive analysis to the global efficacy analysis. Alpha at the final study-specific analysis will be adjusted to incorporate the number of previous global analyses to which the study contributed data in order to control the overall study level type 1 error at 5%. Details will be specified in the study level SAP.

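### The two efficacy censoring rules name different triggers and neither was updated for V19.0, so the supportive final analysis may follow the two arms unequally after unblinding

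*Protocol*

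**What the plan says.** The protocol has two censoring rules for efficacy.

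- **Statistics chapter, section 9.6 (Interim and primary analyses).** After "If a participant receives an approved or licensed COVID-19 vaccine outside of the trial procedures (such as through their workplace) this information will be recorded", it continues: "Participants will be censored in the analysis at the time of their vaccination with the alternative COVID-19 vaccine". The trigger is vaccination. The vaccine is an alternative one, received outside trial procedures. Unblinding is not mentioned.
- **Section 7.6 (Randomisation, blinding and code-breaking).** "Participants will be censored in the analysis of efficacy endpoints at the time of their unblinding and vaccination". The context is participants who ask to be unblinded because the government programme has invited them for an approved or licensed vaccine. The trigger names two events and does not say which date applies when they differ.

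V19.0 added two steps. Section 7.6.1 says "All trial participants will be unblinded following the approval of protocol V19.0", and section 8.11 says "Following unblinding, control participants aged 30 and above will be offered ChAdOx1 nCoV-19 in the approved MHRA 4-to-12 week, 2-dose schedule". The second is scheduled in the Table 14 on unblinding and provision of treatment to controls. Neither step carries an efficacy censoring date. Of the continued follow-up, section 7.6.1 says "This will enable further analysis of immunogenicity, safety and immunological correlate of protection analysis".

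The objectives table in section 4 evaluates the primary endpoint for the whole study. Statistics section 9.7 says "The final study-specific analysis will incorporate all data from the study", calls that analysis supportive, and controls study-level type 1 error at 5%.

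**The concern.** A control given ChAdOx1 nCoV-19 inside the trial has received neither an alternative vaccine nor one from outside trial procedures, so section 9.6 does not reach that person. Section 7.6 may do so, but there the gap depends on the arm. A fully dosed ChAdOx1 recipient who is unblinded under V19.0 has no further COVID-19 vaccination scheduled. If both unblinding and vaccination are needed, that person is never censored, while the vaccinated control is. Controls aged 29 and under are unblinded but not offered a first dose in the trial, so their time also stays open until they are vaccinated elsewhere.

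At stake is the study-level VE at the final analysis. Depending on the rule applied, it could be pulled up by arm-dependent censoring or down by crossover. Symptomatic cases also depend on participants contacting the study team. Section 3.4 justifies the active comparator partly as a guard against biased health-seeking, and that guard ends at unblinding. This last effect cannot be quantified from the documents.

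**Working it through.** **Inputs.** The protocol gives no figure for crossover, post-unblinding person-time or later incidence, so there is no plan figure to reproduce on this point. The power of about 90% in section 9.6 belongs to the pooled primary analysis, comes without a case count, and is not in dispute. Taken from the protocol: VE of 60% (the power assumption in 9.6, so a rate ratio of 0.4), a Poisson model with log time at risk as offset (9.2), and falling transmission at V19.0 (7.6.1). Assumed: 6 months before and 6 months after unblinding; a share x of controls crossing over at unblinding, 0.6 to 0.9; later incidence r relative to earlier, 0.1 to 0.5; VE of 60% in crossed-over controls; equal arms.

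**Step 1: who is censored at V19.0 under each reading?**

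| Participant | 9.6 alone | 7.6, both events needed | 7.6, unblinding suffices |
|---|---|---|---|
| Control vaccinated in the trial | No | At vaccination | At unblinding |
| Fully dosed ChAdOx1 recipient | No | Never | At unblinding |
| Control under 30, not yet vaccinated | No | No | At unblinding |

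Only the last column treats the arms alike, and the text does not select it.

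**Step 2: crossed-over controls retained (9.6 alone).** Person-time is equal in the two arms, so the rate ratio is the ratio of expected cases:

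VE = 1 − 0.4(6 + 6r) / (6 + 6r[(1 − x) + 0.4x])

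- r = 0.1, x = 0.6: 1 − 2.64/6.384 = 58.6%
- r = 0.1, x = 0.9: 1 − 2.64/6.276 = 57.9%
- r = 0.5, x = 0.6: 1 − 3.60/7.920 = 54.5%
- r = 0.5, x = 0.9: 1 − 3.60/7.380 = 51.2%

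Range 51-59%. Without the month split, if f is the incidence-weighted share of control time after crossover, VE = 1 − 0.4/((1 − f) + 0.4f). This gives 57.4% at f = 10%, 52.9% at 25% and 42.9% at 50%.

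**Step 3: vaccinated controls censored, ChAdOx1 arm followed on (7.6, both events needed).** The offset divides cases by person-time:

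VE = 1 − [0.4(6 + 6r)/12] / [(6 + 6r(1 − x))/(6 + 6(1 − x))]

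- r = 0.1, x = 0.6: 1 − 0.220/0.743 = 70.4%
- r = 0.1, x = 0.9: 1 − 0.220/0.918 = 76.0%
- r = 0.5, x = 0.6: 1 − 0.300/0.857 = 65.0%
- r = 0.5, x = 0.9: 1 − 0.300/0.955 = 68.6%

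Range 65-76%.

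**Step 4: does the offset cure it?** With r = 1, the formula in step 3 returns exactly 60% for any x, so unequal follow-up length alone does no harm. The bias needs unequal follow-up and changing incidence together. Section 7.6.1 itself reports falling transmission, and the model terms named in section 9.2 include none for calendar time.

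**Step 5: both arms stopped at unblinding.** VE = 1 − (0.4 × 6)/6 = 60%.

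**The case against.** The strongest reply is that section 7.6 already covers the case. A control unblinded under V19.0 and then vaccinated meets both of its conditions. The adverse-event reporting section (9.6 of the safety chapter) also groups vaccines given to controls in the trial with those of the national rollout. That is a reasonable reading, and it weakens the dilution scenario. It does not settle the ChAdOx1 arm, where it leads to step 3 unless unblinding alone ends follow-up.

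Section 7.6.1 does not list efficacy among the uses of later follow-up. The all-data sentence in 9.7 goes on to say that data already used in the pooled analyses are included, which may be its main purpose. Section 9.2 also restricts efficacy analyses by serostatus, regimen and time since dose. These points stand: a reader might infer that the final analysis will mix unblinded and crossed-over follow-up into VE, but the protocol permits this without stating it.

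The study SAP is not shown and may fix the date. The point does not rest on its absence, because the protocol itself states two different triggers. Statistics section 9.1 has the SAP signed before any interim analysis, and 7.6.1 puts the primary efficacy analysis before V19.0, so a SAP kept to that schedule would need a later amendment to address V19.0.

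Two further inferences should be resisted. One is that the main efficacy result is compromised. Section 9.6 places primary evidence in pooled analyses, 7.6.1 says the primary efficacy analysis was already complete, and 9.7 calls the final analysis supportive. The other is that V19.0 relaxes blinded adjudication of the primary endpoint. That change concerns exploratory disease endpoints only.

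**Conclusion.** The point holds as a conflict between two stated rules, neither of them updated for V19.0. They allow the supportive final analysis to include post-unblinding time that is censored differently by arm. Under the assumptions above, VE would read 65-76% if only vaccinated controls are censored, or 51-59% if crossed-over controls are retained, against a true 60%. The biases run in opposite directions. The upward one depends on incidence falling and would reverse if incidence rose.

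These figures are illustrations. Every input except the 60% is assumed, and the model starts crossover at a single moment, although 7.6.1 says considerable unblinding had already happened. At the mild end of the dilution case the effect is about one percentage point. The protocol does not show that the final VE will be biased. Since 9.7 still controls type 1 error for this analysis, its follow-up period should be unambiguous. Severity: should-fix.

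**What to change.** State one rule, in the same words, in sections 7.6, 9.6 and 9.7. For the primary and secondary efficacy endpoints, follow-up in both arms ends at the earliest of:

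- the participant's own unblinding, including unblinding under V19.0;
- any COVID-19 vaccine outside the randomised course, whether outside the trial, at extra visit B, or under the Table 14 on provision of treatment to controls;
- withdrawal;
- data cut.

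In 9.7, limit the all-data statement to that period for efficacy. Report later cases descriptively by vaccine received, alongside the exploratory non-randomised analysis that 9.6 already foresees. Carry the same rule into the study SAP.

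This changes wording only. No visit, vaccination or safety procedure changes, and no sample size or power figure moves. The cost is post-unblinding person-time and its cases, which would not be randomised, blinded evidence in any event.

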## **9.7 Final Analysis**

A final analysis will be conducted at the end of the study. The final study-specific analysis will incorporate all data from the study, including data that has previously contributed to global efficacy estimates under the pooled analysis strategy. The final analysis will be considered a supportive analysis to the global efficacy analysis. Alpha at the final study-specific analysis will be adjusted to incorporate the number of previous global analyses to which the study contributed data in order to control the overall study level type 1 error at 5%. Details will be specified in the study level SAP.

## **9.8 Procedure for Accounting for Missing, Unused, and Spurious Data.**

All available data will be included in the analysis

## **9.9 Inclusion in Analysis**

All vaccinated participants will be included in the analysis unless otherwise specified in the SAP.

## **9.10 Interim analysis for the combined DSMB**

The independent DSMB will meet regularly to review safety data from all available studies of ChAdOx1 nCoV-19 and will assess whether the assumptions underlying the sample size calculation

are in line with the observed cases. Additionally the independent DSMB will make recommendations based on the interim analyses to assess evidence of efficacy.

## 11 DATA MANAGEMENT

### 11.1 Data Handling

The Chief Investigator will be responsible for all data that accrues from the study.

All study data including participant diary will be recorded directly into an Electronic Data Capture (EDC) system (e.g. OpenClinica, REDCap, or similar) or onto a paper source document for later entry into EDC if direct entry is not available. This includes safety data, laboratory data and outcome data. Any additional information that needs recording but is not relevant for the CRF (such as signed consent forms etc.) will be recorded on a separate paper source document. All documents will be stored safely and securely in confidential conditions.

All adverse event data (both solicited and unsolicited) reported by the volunteer will be entered onto a volunteer's electronic diary card (eDiary) for a maximum of 28 days following administration of the IMP. The eDiary provides a full audit trail of edits and will be reviewed at time-points as indicated in the schedule of events. Any adverse event continuing beyond the period of the diary will be copied into the eCRF and followed to resolution, if there is a causal relationship to the IMP, or to the end of the study if there is no causal relationship.

The participants will be identified by a unique trial specific number and code in any database. The name and any other identifying detail will NOT be included in any trial data electronic file, with the exception of the electronic diaries and household questionnaire, for which consent will be obtained to store the participant email address for quality control purposes. Only site research staff and sponsor data managers have access to view the email address.

The EDC system (CRF data) uses a relational database (MySQL/ PostgreSQL) via a secure web interface with data checks applied during data entry to ensure data quality. The database includes a complete suite of features which are compliant with GCP, EU and UK regulations and Sponsor security policies, including a full audit trail, user-based privileges, and integration with the institutional LDAP server. The MySQL and PostgreSQL database and the webserver will both be housed on secure servers maintained by the University of Oxford IT personnel. The servers are in a physically secure location in Europe. Backups will be stored in accordance with the IT department schedule of daily, weekly, and monthly retained for one month, three months, and six months, respectively. The IT servers provide a stable, secure, well-maintained, and high capacity data storage environment. REDCap and

OpenClinica are widely-used, powerful, reliable, well-supported systems. Access to the study's database will be restricted to the members of the study team by username and password.

If participants consent to provide stool samples; the stool sample (in an anonymised form) will be collected from them by a courier and processed in a laboratory by International Health Management Associates (IHMA), an accredited central laboratory. The sample will then be shipped for analysis by Astra Zeneca in a laboratory in the US. The participant would need to provide their name and address to the courier company.

### **11.2 Record Keeping**

The Investigators will maintain appropriate medical and research records for this trial, in compliance with GCP and regulatory and institutional requirements for the protection of confidentiality of volunteers. The Chief Investigator, co-Investigators and clinical research nurses will have access to records. The Investigators will permit authorised representatives of the Sponsor(s), as well as ethical and regulatory agencies to examine (and when required by applicable law, to copy) clinical records for the purposes of quality assurance reviews, audits and evaluation of the study safety and progress.

Identifiable information such as contact details will be stored for a minimum of 5 years and until the youngest participant turns 21 years. De-identified research data maybe be stored indefinitely. If volunteers consent to be contacted for future research, information about their consent form will be recorded, retained and stored securely and separately from the research data. If volunteers consent to have their samples stored and used in future research, information about their consent form will be recorded, retained and stored securely as per Biobanking procedures and SOP.

### **11.3 Source Data and Case Report Forms (CRFs)**

All protocol-required information will be collected in CRFs designed by the Investigator. All source documents will be filed in the CRF. Source documents are original documents, data, and records from which the volunteer's CRF data are obtained. For this study, these will include, but are not limited to, volunteer consent form, blood results, GP response letters, laboratory records, diaries, medical records and correspondence. In the majority of cases, CRF entries will be considered source data as the CRF is the site of the original recording (i.e. there is no other written or electronic record of data).

In this study this will include, but is not limited to medical history, medication records, vital signs, physical examination records, urine assessments, blood results, adverse event data and details of vaccinations. All source data and volunteer CRFs will be stored securely.

To prevent withdrawal of a participant due to relocation, if there is a nearby participating site and with the consent of the participant, copies of relevant participant research records (such as ICF, paper source documents) will be transferred to the local site using secure email addresses such as nhs.net or by password protected sheets. The electronic research data stored on REDCap will also be transferred to the new site. The original records will be retained by the recruiting site.

#### **11.4 Data Protection**

The study protocol, documentation, data and all other information generated will be held in strict confidence. No information concerning the study or the data will be released to any unauthorised third party, without prior written approval of the sponsor.

#### **11.5 Data Quality**

Data collection tools will undergo appropriate validation to ensure that data are collected accurately and completely. Datasets provided for analysis will be subject to quality control processes to ensure analysed data is a true reflection of the source data.

Trial data will be managed in compliance with local data management SOPs. If additional, study specific processes are required, an approved Data Management Plan will be implemented

#### **11.6 Archiving**

Study data may be stored electronically on a secure server, and paper notes will be kept in a key-locked filing cabinet at the site. All essential documents will be retained for a minimum of 5 years after the study has finished. The need to store study data for longer in relation to licensing of the vaccine will be subject to ongoing review. For effective vaccines that may be licensed, we may store research data securely at the site at least 15 years after the end of the study, subject to adjustments

in clinical trials regulations. Where relevant participants' bank details will be stored for 7 years in line with the site financial policy. De-identified research data maybe be stored indefinitely

General archiving procedures will be conducted in compliance to SOP OVC020 Archiving.

Individual level COV002 data may be shared with COV009, a follow on long-term safety and immunogenicity study, providing participants have consented to this within the COV009 study consent.

